### Participant timeline {13}

Informed consent for the study will be obtained prospectively at the time of the visit corresponding to the pre-transplant evaluation. For patients previously included in the renal transplant waiting list, informed consent will be obtained at the time the patient is called as a potential renal transplant recipient. In either case, once the corresponding consent has been obtained, the patient's clinical history and physical examination will be reviewed and the inclusion–exclusion criteria will be revised. Assignment to treatment will be randomized. The concealment of the randomization sequence will be performed by means of opaque numbered envelopes that will be opened after verifying that the patient meets the inclusion criteria of the study. Assignment to the treatment group will be communicated to the surgeon responsible for the transplant. Follow-up visits will be performed at 3, 6, 12 and 24 months post-transplantation.

The follow-up duration is based on a cohort from our centre consisting of 130 transplant patients during the years 2016 and 2017. This cohort was analysed together with the General and Visceral Surgery team, and we found that 25% of the transplant patients had experienced an incisional hernia within the following 2 years after transplantation. The median time for the development of the incisional hernia was 17.1 months (IQR: 2.6–23 months). Furthermore, the literature supports these timeframes, as most incisional hernias occur within the first 2 years following surgery, particularly when the surgery is elective [16–18].

The following figure shows the template of content for the schedule of enrollment, interventions and assessments (Standard Protocol Items: Recommendations for Interventional Trials (SPIRIT) Figure) (Fig. 1).

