**Methods/design:**

This is a blinded, randomized controlled trial comparing time to incisional hernia over a period of 24 months between patients undergoing kidney transplantation and standardized abdominal closure with or without prophylactic placement of ProGrip™ (Medtronic, Fridley, MN, USA) mesh in an onlay position. As we believe that the mesh intervention is superior to the standard procedure in reducing the incidence of hernia, this is a superiority trial.

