#### Secondary end-points

To determine the safety of mesh reinforcement in laparotomy closure in renal transplantation as measured by determining the incidence of surgical wound complications: number of seromas, number of surgical wound infections, incidence and severity of acute and chronic pain, and need for mesh removal.

To determine the efficacy of mesh reinforcement in laparotomy closure in renal transplantation measured by radiological diagnosis (CT) of incisional hernia at 2 years post-transplantation.

To determine the incidence of surgery for incisional hernia in post-renal transplantation.

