### Outcomes {12}

First outcomeIncidence of incisional hernia at 2 years post-transplantation. Categorical variables (incisional hernia proportion in each group) will be described by absolute and relative frequencies. In addition, differences between groups will be calculated by chi-square test. Time to incisional hernia onset will be described by Kaplan–Meier survival analysis and compared by log-rank test.

Secondary outcomesSafety of mesh reinforcement in laparotomy closure in renal transplantation measured by determining the incidence of surgical wound complications: number of seromas, number of surgical wound infections, incidence and severity of acute and chronic pain, and need for mesh removal. Categorical variables (incisional hernia proportion in each group) will be described by absolute and relative frequencies. In addition, differences between groups will be calculated by chi-square test.Incidence of incisional hernia at 2 years post-transplantation by radiological diagnosis (CT). Categorical variables (incisional hernia proportion in each group) will be described by absolute and relative frequencies. In addition, differences between groups will be calculated by chi-square test. Time to incisional hernia onset will be described by Kaplan–Meier survival analysis and compared by log-rank test.Incidence of surgery for incisional hernia in post-renal transplantation. Categorical variables (incisional hernia surgery proportion in each group) will be described by absolute and relative frequencies. In addition, differences between groups will be calculated by chi-square test. Time to incisional hernia onset will be described by Kaplan–Meier survival analysis and compared by log-rank test.

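### The time-to-event analyses do not match how events are observed: wrong event for surgery, no onset time from a 2-year CT, and exact-time methods for hernias found at visits

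*Protocol article*

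**What the plan says.** Outcomes {12} of the protocol article gives the primary outcome as "Incidence of incisional hernia at 2 years post-transplantation", described as a proportion in each arm, and adds: "In addition, differences between groups will be calculated by chi-square test". Sample size {14} rests on the same 24-month proportions, 20% against 5%, with 76 per group.

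Beside the chi-square test stands a time analysis: "Time to incisional hernia onset will be described by Kaplan–Meier survival analysis and compared by log-rank test". Outcomes {12} uses this sentence three times without change: for the primary outcome, for hernia by CT, and for surgery for hernia. In the surgery paragraph the proportion has been relabelled as a surgery proportion, but the time sentence has not. Statistical methods {20a} repeats the sentence and adds stratification by obesity. The abstract (Methods/design) presents the trial as "comparing time to incisional hernia over a period of 24 months between patients undergoing kidney transplantation".

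Under Secondary end-points, the CT outcome is efficacy "measured by radiological diagnosis (CT) of incisional hernia at 2 years post-transplantation"; Outcomes {12} gives the same time point.

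Participant timeline {13} states: "Follow-up visits will be performed at 3, 6, 12 and 24 months post-transplantation". It also reports the centre's own cohort of 130 transplant patients, 25% of whom had a hernia within 2 years: "The median time for the development of the incisional hernia was 17.1 months", with an interquartile range of 2.6 to 23 months.

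**The concern.** Kaplan–Meier and log-rank, as named, take each event to have its own date. The three outcomes are observed in three different ways.

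- **Surgery** has a true date, but the plan analyses a different event, hernia onset. Followed literally, the surgery outcome has no time analysis of its own and repeats the primary one.
- **CT at 2 years** shows whether a hernia is present, not when it began. A time-to-onset curve from such scans would consist of detections at about month 24.
- **Hernia found at a visit** is known only to have arisen since the previous visit. The widest interval, months 12 to 24, is where the centre's own data put most onsets.

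At stake is what the published curves would mean. The abstract puts time to hernia in the foreground, yet the shape of the curve, and any onset time read from it, would largely reflect the visit schedule.

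**Working it through.** **1. The plan's own figure.** Two-sided alpha 0.05, power 80%, 20% against 5%, pooled variance, no continuity correction; mean proportion 0.125:

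n = [1.960 × √(2 × 0.125 × 0.875) + 0.842 × √(0.20 × 0.80 + 0.05 × 0.95)]² / 0.15² = (0.917 + 0.383)² / 0.0225 ≈ 75.1, rounded up to **76**.

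This reproduces the stated size (power at 76 is 80.5%). It uses no onset times, so nothing below changes it.

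**2. Surgery and CT.** No arithmetic is needed. The surgery paragraph names surgery in its outcome and its proportion, and hernia onset in its time analysis. The CT outcome is tied to 2 years in both places that define it, yet it is given an onset-time analysis.

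**3. Share of onsets in the 12–24 month gap.** Take the cohort quartiles (2.6, 17.1 and 23 months) as describing hernias within 2 years, as the preceding sentence suggests. Half then arise at or after 17.1 months, so at least 50% fall between the month-12 and month-24 visits. With linear interpolation (an assumption), the share by month 12 is 0.25 + 0.25 × (12 − 2.6)/(17.1 − 2.6) = 0.412, leaving about 59% in the gap.

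**4. Effect on the curve between visits.** With a true control rate of 20% and detection only at visits, the curve stays at 0.412 × 20% = 8.2% from month 12 until the month-24 visits. At month 23 the true figure is 0.75 × 20% = 15%.

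**5. Effect at month 24.** Simulation of 1,500 trials per setting, 76 per arm, 20% against 5%, onsets drawn from the interpolated quartiles. Each hernia is dated to the first visit after onset. The visit scatter is assumed.

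| Event time used | Control-arm Kaplan–Meier at month 24.0 |
|---|---|
| Nominal visit time | 19.9% |
| Nominal, 10% dropout | 20.0% |
| Actual date, ±0.5 month | 15.4% |
| Actual date, ±1 month | 14.5% |

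A hand approximation agrees. Entering the month-24 window, 91.8% are event-free, and 11.8/91.8 = 0.129 of those attending have a hernia. Once half have attended, the estimate is 1 − 0.918 × exp(−0.129 × ln 2) ≈ 16%. The simulated values are slightly lower because early visits miss some late onsets.

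**6. Effect on the tests.** The settings were those above plus visits all up to 1 month late or all up to 1 month early. Log-rank type I error (both arms at 20%) was 4.1% to 5.6%. Log-rank power was 75% to 82%, against 81% to 84% with exact onset times. Chi-square power was 78% to 84%. The Monte Carlo standard error is about √(0.8 × 0.2/1500) = 1.0 point for power and √(0.05 × 0.95/1500) = 0.6 point for type I error.

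**The case against.** The strongest reply is that the headline result does not depend on onset dates. The 24-month incidence is planned as a proportion with a chi-square test, and nothing in the article says it will be read from the curve. That stands. A reader might infer that the trial's 24-month incidence will be wrong, or that the curve will end near 50% in the control arm. The simulation does give 52–53% at the far end of the curve with scattered visit dates, but only after nearly everyone has been censored, and the plan does not call for that value. With nominal visit times the month-24 estimate is right. The documents support neither inference.

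Second, the article does not say that visit dates will serve as onset dates. Study setting {9} draws on clinical notes and imaging from follow-up, and the cohort quartiles do not fall on the 3, 6, 12 and 24 month grid. Some hernias may therefore be dated between visits. This softens the point without removing it: a first record in the notes is still a detection date, and hernias found at scheduled visits remain interval-censored.

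Third, visit windows and dating rules commonly belong in the SAP. Data access {31c} mentions one, and it is not shown. Their absence is not held against the article. The point concerns what the article does fix: the event and the method.

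Fourth, the 2-year phrase for CT could mean a follow-up horizon, as it does for the primary outcome, and the SPIRIT figure is not shown. So it would be too strong to say that the CT outcome cannot have onset times; the CT point is conditional on that figure.

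None of these replies touches the surgery outcome.

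**Conclusion.** The concern holds for the match between method and data, in three parts of unequal certainty.

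- **Surgery:** wrong as written, with no assumption needed.
- **CT:** inconsistent on the text shown, unless the schedule figure provides scans before 2 years.
- **Primary time analysis:** hernias found at visits are interval-censored, and at least half of onsets by 24 months (about 59% under interpolation) fall in one 12-month gap. The curve between visits is then not a curve of onset: 8.2% against 15% at month 23 if all detection is at visits.

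The 24-month proportion, the chi-square test, the 76 per group and the log-rank type I error are not materially affected, and the loss of log-rank power is small. The Kaplan–Meier value at month 24 is distorted only if scattered actual visit dates are used as event times; the 14.5–15.4% figures rest on that assumption and on assumed windows of 0.5 to 1 month. The change should be made, but it does not threaten the primary comparison.

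**What to change.** In Outcomes {12}, with matching wording in Statistical methods {20a}:

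1. **Surgery outcome:** replace time to hernia onset with time from transplantation to hernia surgery. Kaplan–Meier and log-rank then suit it.
2. **CT outcome:** analyse as a proportion only, and drop Kaplan–Meier and log-rank. If earlier CTs are scheduled, state them and define the time analysis on those scan times.
3. **Primary outcome:** keep the 24-month proportion and chi-square test as the headline. Analyse time on the scheduled grid (3, 6, 12, 24 months) with a grouped-time or interval-censored method, for example a Turnbull curve with a complementary log-log model, stratified by obesity as {20a} already plans. Assign each assessment to its nominal visit, so that scatter around month 24 cannot distort the estimate.

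The cost is revised wording and minor programming. No extra visits, data or patients are needed.

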**Fig. 1 Fig1:**
[figure not shown]
SPIRIT Figure

### Sample size {14}

For the primary endpoint (incisional hernia at 24 months), assuming a proportion in the control group of 20%^1^ and a proportion of 5% in the intervention group (prophylactic mesh reinforcement placement), with an alpha level of 0.05 and power of 80%, the sample size per group was calculated at 76 patients.

### Recruitment {15}

Study background, objectives, interventions and assessments will be explained in detail at the time of the visit corresponding to the pre-transplant evaluation, before the informed consent is collected and after all questions have been adequately answered.

## Assignment of interventions: allocation

### Sequence generation {16a}

Given the difficulty of ensuring equality of sample size between the experimental and control groups in trials with small sample size and two arms (intervention-control), a stratified allocation by the variable obesity (BMI > 30), which is a determinant risk factor in the response to the intervention, will be carried out using permuted blocks of variable size in each stratum (blocks of 2, 4 or 6 permutations) generated by the hospital’s Clinical Biostatistics Unit.

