## Methods: participants, interventions and outcomes

### Study setting {9}

Unicentric study carried out at an academic hospital. The source of information will be constituted by the Electronic Clinical History of the Hospital Centre in what refers to the clinical notes of the physicians responsible for the care of the patients, laboratory data and radiological explorations carried out in the follow-up of the patients.

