### Who will take informed consent? {26a}

Informed consent for the study will be obtained prospectively at the time of the visit corresponding to the pre-transplant evaluation by the Principal Investigator or, as authorized surrogates, any member of the Kidney Transplant Surgery Team after complete explanation of study conditions to potential recipients of a first kidney transplantation. For patients previously included in the kidney transplant waiting list, informed consent will be obtained at the time the patient is called as a potential renal transplant recipient, after revision of inclusion and exclusion criteria. When a patient signs the written informed consent, they are enrolled in the study.

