### Concealment mechanism {16b}

To guarantee the concealment of the randomization sequence, the randomization codes will be kept in opaque envelopes with correlative numerical identification that will be opened once it has been verified that the patient meets the inclusion criteria and has signed the informed consent form.

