### Implementation {16c}

Allocation sequence will be generated by the hospital’s Clinical Biostatistics Unit. Participants will be enrolled by the principal investigator ([name]) and all the members of the transplant surgery team ([name], [name], [name], [name], [name]). Each transplant surgery team member will review patient’s informed consent, clinical history and physical examination and inclusion–exclusion criteria will be revised on the day of transplantation. An opaque numbered envelope stratified by BMI prepared by the hospital’s Clinical Biostatistics Unit will be opened by a member of the surgical transplant team on call and the treatment group communicated to the surgeon responsible for the transplant.

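### Stated blocks of 2, 4 or 6, in a single-centre trial whose unblinded surgical team consents patients and opens the envelopes, weaken allocation concealment: up to about 70% of next allocations could be guessed

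*Protocol article*

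**What the plan says.** All references are to the protocol article.

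- **Setting.** Study setting {9}: "Unicentric study carried out at an academic hospital".
- **Sequence.** Sequence generation {16a} specifies "a stratified allocation by the variable obesity (BMI > 30") with "permuted blocks of variable size in each stratum (blocks of 2, 4 or 6 permutations"). The list comes from the hospital's Clinical Biostatistics Unit. The stated reason is the difficulty of obtaining equal arms in a small two-arm trial.
- **Concealment.** Concealment mechanism {16b} uses opaque, consecutively numbered envelopes, opened only after eligibility is confirmed and consent signed. Their purpose is given as "To guarantee the concealment of the randomization sequence".
- **Enrolment.** Implementation {16c}: "Participants will be enrolled by the principal investigator" and the members of the transplant surgery team, who also re-check consent and eligibility on the day of transplantation.
- **Opening.** In the same section, the BMI-stratified envelope "will be opened by a member of the surgical transplant team on call and the treatment group communicated to the surgeon responsible for the transplant".
- **Consent.** Who will take informed consent? {26a} gives this task to the principal investigator or "any member of the Kidney Transplant Surgery Team after complete explanation of study conditions". It is normally done at the pre-transplant evaluation. For patients already on the waiting list, "informed consent will be obtained at the time the patient is called as a potential renal transplant recipient".
- **Blinding.** Who will be blinded {17a} lists participants, outcome assessors and the analyst. Surgeons are not listed and could not be, since they place or omit the mesh.

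**The concern.** Opaque envelopes protect against reading the next code. They do not protect against inferring it. In a permuted block the arms must even out within a few patients, so whoever knows the running count in a stratum has information about the next envelope. The smaller the block, the stronger that information; in a block of 2 the second allocation is fixed by the first.

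Here the people best placed to know the count also decide whether to ask a patient for consent. The eligibility criteria are broad (adult, first transplant, consent given), so the approach for consent is the main discretionary step. For waiting-list patients it happens at the call for transplant, when the next envelope in the stratum is already the one that patient would receive.

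A reason to prefer one arm for a given patient could arise in either direction. Trial design {8} states a belief that mesh is superior, and the Discussion raises infection risk with mesh under immunosuppression. If the expected arm influences who is approached, even unconsciously, the arms differ in prognosis before surgery. Masking the patient and the assessor cannot undo that. Nor can the intention-to-treat analysis, which contains only patients who were randomized and transplanted.

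**Working it through.** **The plan's own figure.** The article gives no figure for predictability. It does fix the trial size: 20% versus 5%, alpha 0.05, power 80%, 76 per group. With the pooled two-sided formula and mean proportion 0.125:

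n = [1.960·√(2·0.125·0.875) + 0.842·√(0.20·0.80 + 0.05·0.95)]² / 0.15² = (0.917 + 0.383)² / 0.0225 ≈ 75.1, rounded up to 76.

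The figure reproduces, so the total is 152. The present point concerns bias and does not affect it.

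**Inputs for predictability.** From {16a}: block sizes 2, 4 and 6, and two BMI strata. Assumed, because not stated: equal probability of the three sizes; 25% obese (range 10–40%); and how much of the past a team member knows (varied below).

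**Full history known.** While the arms in a stratum are level, the next allocation is a coin toss. Otherwise the best guess is the arm that is behind. For a block of size 2m the expected number of coin-toss positions is 4^m / C(2m, m) − 1, and the expected number of correct guesses is m plus half of that.

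| Block size | Coin tosses | Correct guesses | Correct, % |
|---|---|---|---|
| 2 | 1.000 | 1.500 | 75.0 |
| 4 | 1.667 | 2.833 | 70.8 |
| 6 | 2.200 | 4.100 | 68.3 |
| 8 | 2.657 | 5.329 | 66.6 |

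Mixing 2, 4 and 6 equally (12 patients per three blocks):

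- correct: (1.500 + 2.833 + 4.100) / 12 = 70.3%
- coin toss: (1.000 + 1.667 + 2.200) / 12 = 40.6%

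Simulation of 152 patients in two strata agrees: 70.1% correct, 41% coin toss. It also gives 59% of allocations predictable with at least 75% certainty and about 4% certain. Changing the obese share from 10% to 40% leaves correct guesses at about 70%. Unequal block-size mixes give 69.4% (large blocks more frequent) to 71.1% (small blocks more frequent).

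**Partial history known (simulation, equal mix).**

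| Share of past allocations known | Correct, % | Predictable at ≥75%, % |
|---|---|---|
| all | 70 | 59 |
| three quarters | 63 | 27 |
| half | 59 | 12 |
| one third | 56 | 5 |
| one sixth | 54 | 1 |

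Knowing only the last allocation in the stratum and guessing the opposite is right in (1·1 + 3·2/3 + 5·3/5 + 3·1/2) / 12 = 7.5 / 12 = 62.5% of cases.

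**Alternatives, full history known.**

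- *Blocks 4, 6 and 8:* (2.833 + 4.100 + 5.329) / 18 = 68.1% correct (67.4–67.8% in simulation). The share at 75% certainty or more is about 35%.
- *Big-stick rule, limit b = 3 per stratum:* a share 1/(2b) = 16.7% of allocations is forced in the long run (15–16% in simulated strata of 32 and 120). Correct guesses are 0.5 + 1/(4b) = 58.3%.

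**The case against.** **Knowledge of the past is assumed.** A reader might infer that the surgeons see every past allocation. The article does not say so. Implementation {16c} has one on-call member open the envelope and tell the operating surgeon; it mentions no shared log. This stands, and it is why the result is a range. Near-complete knowledge is still plausible. The outcome assessor has to agree not to look up the assignment in the surgical record, so it is recorded there, and no such undertaking is described for the enrolling surgeons.

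**The envelopes still work.** A reader might also infer that the opaque envelopes fail to conceal the sequence, or that most allocations are as good as known. Neither is supported. The next code stays hidden until eligibility and consent are settled. Even with full history about 41% of allocations are a coin toss and only about 4% are certain. Varying the block size is a real protection: fixed blocks of 4 would make about 33% certain. It removes certain guesses, however, and not the average predictability.

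**The opportunity is limited.** Eligibility is objective, and patients who consent at the pre-transplant evaluation do so before their place in the sequence is known. That leaves less room for selection. Late consent covers only patients already on the waiting list, and their share is not given.

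**The remedy gains little on average.** Moving to 4, 6 and 8 lowers correct guesses only from 70% to 68%, and the fall from 59% to 35% depends on the 75% cut-off: at 70% the shares are 59% and 60%. This also stands. The change is worth making because it is nearly free, not because it removes the problem.

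**Conclusion.** The concern holds as a weakening of concealment. {16a} fixes small blocks, including size 2, in a trial where one unblinded team in one centre consents, re-checks eligibility and opens the envelopes. Under equal block-size probabilities, correct guesses run from about 54% (one sixth of the history known) through 59% (half known) to 70% (all known), against 50% for an unpredictable sequence. The upper end needs no modelling and no knowledge of the block sizes: picking the arm that is behind in the stratum does as well as the best possible guess.

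The documents do not establish that any surgeon holds the full history, that consent would be withheld on the strength of a guess, or how many patients consent late. The size of any resulting bias therefore cannot be stated. What can be said is that {16b} claims a guarantee that the block design does not support. The sample size is unaffected.

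**What to change.** In Sequence generation {16a}, drop blocks of 2 and use larger random sizes, for example 4, 6 and 8. State in the protocol only that sizes vary at random. Keep the sizes in a document held by the Clinical Biostatistics Unit and out of what the enrolling team sees. In {16b}, replace the claim of a guarantee with a description of the measure. Optionally, release allocations through the REDCap system already in use instead of envelopes opened by the team. If recruitment has begun, a new list can replace the unopened envelopes.

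**Cost.** A new list and a short wording change. The largest possible difference between arms rises from 3 to 4 per stratum, or from 6 to 8 overall. At worst that is 72 versus 80 patients, equivalent to 2·72·80 / 152 = 75.8 per arm instead of 76, so the loss of power is negligible.

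**Limits.** Withholding the sizes prevents confident calculation but not the simple rule of guessing the arm that is behind.

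**An option with a trade-off.** A big-stick rule with limit 3 lowers correct guesses to about 58%, but makes about 16% of allocations certain to anyone who knows the limit and the running count, against about 4% now. It is defensible only if the limit is withheld from the team.
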